### Setting and Participants

Makeni is the largest city in the Northern Province of Sierra Leone. The city is the capital of Bombali District, and is the economic center of the Northern Province. Makeni is the Provincial Headquarters of the Northern Province of Sierra Leone. The total population is 125,970, of which 124,634 live in urban areas and 1336 live in rural areas [24]. The most common forms of employment are agriculture and trade. Krio is the primary language.

Inclusion criteria for CHW participation in problem analysis and UI/UX testing are as follows: currently providing maternal and child health services to families with children aged 6-36 months in the Makeni region, aged 18 or older, and ability to attend three 90-minute sessions. Inclusion criteria for supervisors are as follows: currently providing supervision to CHWs delivering the aforementioned services in the Makeni region and aged 18 or older. We will exclude individuals who do not meet CHW or supervisor inclusion criteria.

Inclusion criteria for families are as follows: (1) a Sierra Leonean household with cohabitating caregivers (eg, father/mother, mother/grandmother, mother/partner) and child (aged 6-36 months) with both caregivers aged 18 or older; and (2) 1 caregiver scoring at least 62.5 on the Difficulties in Emotion Regulation Scale (DERS). Both caregivers must agree to attend FSI-ECD sessions; however, if 1 caregiver decides to withdraw, the family can still continue to participate. If enrolled families have more than 1 child aged 6-36 months, we will include all eligible children as study participants. We will exclude families who do not meet all inclusion criteria or who experience active family crises (eg, current suicidality or psychosis, serious medical condition, or cognitive impairment as assessed by a study social worker).

We will recruit families from 2 communities within the Makeni region in coordination with the CHW Focal Person, who is the Ministry of Health and Sanitation Community Health Worker Program official responsible for coordinating the work of CHWs and supervisors within peripheral health units. Peripheral health units are key units within the Sierra Leone health care system. They deliver “first-line” care, including prenatal care, routine deliveries, immediate postnatal and neonatal care, community outreach services, routine vaccination, and treatment of childhood illnesses and malnutrition. Peripheral health units maintain records of families in the community who have sought services and we will be able to identify families with a child aged 6-36 months by reviewing their records. We anticipate that engaging at the community level with the peripheral health units will facilitate recruitment and enrollment of our target sample size.

We will recruit CHWs (N=8) and supervisors (N=2) from the 2 identified peripheral health units to deliver the mHealth-supported FSI-ECD and provide weekly supervision. CHW is a volunteer position and there are no educational qualifications that must be met in order to be engaged as a CHW. CHWs and supervisors who participate in problem analysis and UI/UX sessions will be eligible to participate in the FSI-ECD pilot study. Inclusion criteria are CHWs assigned to the peripheral health unit that provides health services in 1 of the 2 communities and 18 years or older. We will exclude CHWs who do not meet inclusion criteria. Inclusion criteria for supervisors are currently overseeing CHWs providing maternal and child health services in 1 of the 2 communities and aged 18 or older. We will exclude supervisors who do not meet inclusion criteria.

### FSI-ECD

The FSI-ECD is composed of 4 core components: (1) developing problem-solving, stress management, and emotion regulation skills; (2) cultivating positive parenting skills and fostering father/male co-caregiver engagement; (3) developing communication and conflict resolution skills; and (4) exploring alternatives to harsh punishment and practicing nonviolent child discipline. The FSI-ECD integrates key elements of the evidence-based Family-Based Prevention Intervention [25] and was culturally adapted to the Rwandan context through extensive community-based participatory research methods involving Rwandan community advisory boards. The FSI-ECD is delivered in 12 modules in the home via coaching by CHWs. Sessions are delivered once per week and last approximately 90 minutes. Prior to the trial, we will adapt the FSI-ECD to the cultural context of Sierra Leone. A Community Advisory Board will advise on local parenting and mental health terms and concepts drawing from previously collected qualitative data on parenting in Sierra Leone.

### Standard Services

Standard CHW care involves 3 home-visiting, educational sessions delivered to families following childbirth, with weekly supervision via phone or face-to-face. Topics of home-visiting sessions include skilled postnatal care for mothers, early initiation of breastfeeding, nutrition, immunization services, handwashing and hygiene practices, building the capacity of family members to take care of newborns and children under age 5. CHWs also conduct screenings for acute malnutrition and growth monitoring to identify early referrals, and they can provide family planning methods; deworming tablets; and other vitamins for acute malnutrition, dehydration, and antimalaria treatment. Each home-visiting session lasts approximately 60 minutes.

### Training and Supervision

CHWs and supervisors will be trained in the core components of the adapted FSI-ECD by FSI-ECD experts. Training will occur 5 days per week over the course of 3 weeks. At the conclusion of training, CHWs and supervisors will complete a competency assessment. CHWs and supervisors will also complete a 1-day technology training on use of the mHealth tools. During FSI-ECD delivery, CHWs and supervisors will participate in weekly 60-minute supervision sessions guided by mHealth tools to support delivery quality. CHWs and supervisors will complete fidelity monitoring checklists that are embedded in mHealth tools, and review of fidelity monitoring data will inform quality improvement feedback cycles during supervision.

### Measures

#### FSI-ECD Outcomes

We will collect quantitative data on caregiver mental health and emotion regulation, harsh parenting practices, the home environment, and family functioning at baseline, postintervention, and 3-month follow-up. All quantitative measures have undergone a thorough development, translation, and validation process [26] in a prior randomized controlled trial in Sierra Leone. The following quantitative measures will be used: the DERS (α=.95) [27], WHO Disability Assessment Schedule (α=.91) [28], the Conflict Tactics Scale (α=.72-.86) [29], Hopkins Symptom Checklist (α=.92) [30], and Post-traumatic Stress Disorder Reaction Index (α=.93) [31]. To assess caregiver–child interactions, we will use the Home Observation for Measurement of the Environment (α=.73) [32] and the Observation of Mother–Child Interaction (α=.83) [33]. We will also collect qualitative data at postintervention via key informant interviews with randomly selected caregivers (4 males/4 females) to assess FSI-ECD feasibility, acceptability, and satisfaction.

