**Objective:**

This study aims to (1) apply a user-centered design to develop and test mHealth tools to improve supervision and fidelity monitoring of community health workers (CHWs) delivering the FSI-ECD and (2) conduct a pilot randomized controlled trial of the FSI-ECD to assess feasibility, acceptability, and preliminary effects on caregiver mental health, emotion regulation, caregiving behaviors, and family violence in high-risk families with children aged 6-36 months in comparison with control families receiving standard care.

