**Methods:**

We will recruit and enroll CHWs, supervisors, and families with a child aged 6-36 months from community health clinics in Sierra Leone. CHWs and supervisors will participate in 1 problem analysis focus group and 2 user interface/user experience cycles to provide feedback on mHealth tool prototypes. Families will be randomized to mHealth-supported FSI-ECD or standard maternal and child health services. We will collect quantitative data on caregiver mental health, emotion regulation, caregiving behaviors, and family functioning at baseline, postintervention, and 3-month follow up. We will use a mixed methods approach to explore feasibility and acceptability of mHealth tools and the FSI-ECD. Mixed effects linear modeling will assess FSI-ECD effects on caregiver outcomes. Cost-effectiveness analysis will estimate costs across FSI-ECD versus standard care.

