### Study Objectives

The current study aims to (1) pilot a culturally adapted version of the FSI-ECD delivered by CHWs to vulnerable Sierra Leonean families with children aged 6-36 months to assess feasibility, acceptability, and preliminary effects of mHealth-supported delivery of the FSI-ECD on caregiver mental health and emotion regulation, caregiver–child interactions, and family violence in comparison to control families who receive standard care with standard supervision; and (2) develop and pilot innovative and cost-effective mHealth tools to support CHW delivery of the FSI-ECD. Development of mHealth tools will employ a user-centered design approach to design, prototype, and test digital tools that incorporate user feedback from supervisors and CHWs at each stage of development. User-centered design grounds the tool/app development process in the needs and preferences of those who will use the tool to make it more user-friendly, acceptable, and suitable to the real-world needs of the user; it creates a sense of engagement and shared ownership that aids adoption of the innovation [17-19]. We will use participatory methods and best practices in the user interface/user experience (UI/UX) design to engage CHWs and supervisors in the iterative development process to ensure that our mHealth tools and strategies meet their needs, align with local technological capacity and health service priorities, and support sustained evidence-based practice. The objectives are to develop mHealth tools for supervision, fidelity monitoring, and training of CHWs in Sierra Leone and to provide supervisors with quick visual data displays on CHW performance to inform quality improvement cycles. We will also conduct a preliminary cost-effectiveness analysis to assess the economic value of the mHealth-supported delivery of the FSI-ECD versus standard care with standard supervision.

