#### mHealth Outcomes

We will collect quantitative data on mHealth tool feasibility, acceptability, adoption, and appropriateness with CHWs and supervisors at baseline and postintervention via quantitative scales developed by researchers at Johns Hopkins Bloomberg School of Health [34]. We will track length of time to deliver FSI-ECD content, use of embedded fidelity monitoring and tracking features, and amount of CHW–supervisor contact via tablet, phone, and face-to-face. Fidelity data will include a CHW-completed electronic fidelity checklist designed to support self-monitoring and performance review with supervisors as well as a supervisor-completed electronic fidelity checklist to be completed while reviewing audiotaped FSI-ECD sessions and discussed during supervision. We will also collect data on mHealth tools postintervention via key informant interviews with CHWs (n=8) and supervisors (n=4) to understand usability of audio/video functions for FSI-ECD delivery, supervision, and quality improvement cycles.

Participant diagnostic and assessment data will be collected via tablets and deidentified. All tablets will be encrypted and password protected using a password known only to the research team. All data on the tablet will remain on the tablet until it is connected to Wi-Fi and uploaded to a secure server. Daily quality assurance and data monitoring checks will determine successful upload of the data, which will be backed up to Box, a secure, HIPAA (Health Insurance Portability and Accountability Act)-compliant, cloud-based storage platform, before it is remotely wiped from the tablet.

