## Discussion

### Possible Challenges

There are several potential challenges that may arise during study implementation. In Sierra Leone, many caregivers are involved in employment that requires a high level of daily mobility, such as trade and agriculture. Some caregivers travel across districts, regions, or to neighboring countries for several weeks in order to work. In this work context, we may experience some challenges recruiting and retaining caregivers because participation in the FSI-ECD requires caregivers to attend twelve 90-minute sessions delivered once per week. Although the FSI-ECD may provide long-term benefits for caregiver mental health and child development, these benefits may not be a sufficient incentive for study participation. To help address this challenge, we will encourage highly flexible scheduling to accommodate the working hours of caregivers. The home-visiting nature of the FSI-ECD is also intended to improve service access for families with young children and will relieve the burden of traveling to attend services.

Technology literacy levels and potential technical issues that may occur with the mHealth tools could also pose challenges to this study. To address this, we will provide a 1-day technology literacy training on the use of mHealth tools and basic skills with tablet use. We will also provide ongoing technical support to troubleshoot any technical issues. It is possible that poor connectivity may impede rapid resolution of technical issues, because technical assistance will be remote. However, given that CHWs and supervisors will not need to use mHealth tools on a daily basis, our team should be capable of reasonably resolving any issues with enough time to ensure study activities proceed as planned. We will also train the study data manager in use of the mHealth tools to support greater in-country expertise. We will document any technical issues and keep a log of the strategy to resolve them in the event that the same issue is encountered on a subsequent occasion. To address potential difficulties with internet connectivity, we will place a modem for CHWs and supervisors in the peripheral health unit where they are based. Battery-powered tablets with offline functions and access to cloud storage will also ensure that mHealth tools can be feasibly used and data securely stored until connectivity is available.

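### The eight caregiver interviews, the only stated family-side assessment of FSI-ECD feasibility and acceptability, are drawn without regard to attendance, although the protocol expects attendance and retention problems.

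*Protocol article*

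**What the plan says.** In the Abstract (Objective), the pilot trial is there "conduct a pilot randomized controlled trial of the FSI-ECD to assess feasibility, acceptability, and preliminary effects", and Study Objectives repeats this as aim (1). The Abstract (Methods) states: "We will use a mixed methods approach to explore feasibility and acceptability of mHealth tools and the FSI-ECD".

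The Measures section then assigns data to these aims.

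- **Families, quantitative (FSI-ECD Outcomes):** "caregiver mental health and emotion regulation, harsh parenting practices, the home environment, and family functioning". These are clinical and parenting outcomes. None is a feasibility or acceptability scale.
- **Families, qualitative (same section):** "key informant interviews with randomly selected caregivers (4 males/4 females) to assess FSI-ECD feasibility, acceptability, and satisfaction", at postintervention.
- **CHWs and supervisors (mHealth Outcomes):** "quantitative data on mHealth tool feasibility, acceptability, adoption, and appropriateness with CHWs and supervisors". These scales concern the tool, not the families' experience of the intervention.
- **Process data (mHealth Outcomes):** "We will track length of time to deliver FSI-ECD content, use of embedded fidelity monitoring and tracking features", together with CHW–supervisor contact and fidelity checklists.

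Two other places bear on who should be interviewed. Possible Challenges warns that "we may experience some challenges recruiting and retaining caregivers because participation in the FSI-ECD requires caregivers to attend twelve 90-minute sessions", and adds that some caregivers are away for weeks at a time for work. Setting and Participants allows a family to remain in the study when one of its two caregivers withdraws.

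**The concern.** The caregivers who can explain missed sessions are those who missed them. They are probably a minority, and a random draw of eight does not ensure that any of them is interviewed. The one-caregiver rule adds to this: a family can count as participating while one caregiver, perhaps the father or male co-caregiver whose engagement is part of a core component, has stopped attending.

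The pilot's statement on feasibility and acceptability to families could then rest on interviews that contain no account of the one difficulty the article predicts. Whether caregivers can attend twelve weekly sessions, and why some cannot, is what a larger trial would most need to learn from this pilot.

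**Working it through.** **No plan figure for the interviews.** The article gives no derivation for eight interviews, so there is nothing to reproduce on that count.

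**Inputs**

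- 80 families with 2 respondents each on average (Data Analysis).
- 8 interviews, 4 men and 4 women (FSI-ECD Outcomes).
- Assumed: equal allocation, so 40 FSI-ECD families and 80 FSI-ECD caregivers; interviews confined to that arm; 40 men and 40 women for the calculation by sex. Mother/grandmother pairs would change that last split.
- Assumed: 10%, 20% or 30% of caregivers disengaged. No rate is stated.

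**Consistency check on 40 per arm.** With 4 observations per family and a within-family correlation of 0.5, the variance factor is (1 + 3 × 0.5)/4 = 0.625. For an effect of 0.50, the standard error is √(2/40 × 0.625) = 0.177, and 0.50/0.177 − 1.96 = 0.87, which gives power 0.81. The article states 0.80, so equal arms fit its own figure. This does not prove equal allocation.

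**Chance that no interviewee is disengaged.** With D disengaged among 80 and 8 drawn at random:

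P(none) = C(80 − D, 8) / C(80, 8)

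With the draw made separately by sex and d disengaged among 40 of each sex:

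P(none) = [C(40 − d, 4) / C(40, 4)]², where C(40, 4) = 91,390

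| Disengaged | 8 of 80 | 4 of 40 men and 4 of 40 women |
|---|---|---|
| 10% | 0.413 | (58,905/91,390)² = 0.415 |
| 20% | 0.153 | (35,960/91,390)² = 0.155 |
| 30% | 0.049 | (20,475/91,390)² = 0.050 |

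Drawing by sex makes almost no difference. The expected number of disengaged interviewees is 8 × the rate: 0.8, 1.6 and 2.4. The chance of at most one is 0.82, 0.50 and 0.24.

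**Disengagement among men only.** The four men drawn include none of the disengaged men with probability 0.645, 0.393 and 0.224 at 10%, 20% and 30% of men, the unsquared terms above.

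**Reachability.** All these figures assume that every selected caregiver can be interviewed. If absent or withdrawn caregivers are harder to reach, the chances of missing them are higher. The documents give nothing from which to say by how much.

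**Under a stratified draw.** If at least one interview per sex is reserved for the low-attendance stratum, the chance of hearing from none is zero whenever that stratum is not empty and someone in it can be interviewed. Two of eight is 25% of the interviews, close to proportional at the middle of the assumed range.

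**The case against.** Several counter-arguments have force.

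- **Disengagement would not be invisible.** A reader might infer that it could go wholly unnoticed. The article does not support that. Families lost to assessment appear as missing outcome data at postintervention or 3 months, sessions are audiotaped, and fidelity data are reviewed weekly. What is easily missed is one caregiver's absence in a family that continues, and the reasons behind any absence.
- **Attendance and retention endpoints may exist elsewhere.** A reader might also infer that the pilot lacks them, or lacks progression criteria. This is a condensed article, its schedule figure is not shown, and such detail commonly sits in the full protocol. Their absence here is not a finding.
- **The interviews are not restricted to completers.** Postintervention is a time point, not an eligibility condition, and a caregiver who withdrew may still live in a reachable household. That interviewees would be mostly retained and satisfied is conjecture.
- **Eight interviews can suffice for themes.** They are not meant to estimate a rate, so their number is not the fault.
- **Random selection protects against hand-picked favourable informants.** This is a real merit, and the remedy should keep it.
- **The size depends on the rate.** At 20% or 30% disengagement, a random draw includes at least one disengaged caregiver with probability about 85% or 95%. The large chance of missing them arises at 10%, where feasibility is least in doubt.
- **The risk is mitigated.** Flexible scheduling and home delivery are planned.

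These points narrow the concern to the rule for choosing interviewees. On that, the text is explicit: selection is random, balanced only by sex, and these interviews are the only stated source on feasibility and acceptability from families.

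**Conclusion.** The point holds as a mismatch between a stated method and a stated risk. The interviews ignore attendance although the article expects attendance to be the difficulty. Under an assumed frame of 80 FSI-ECD caregivers, the chance of hearing from no disengaged caregiver is about 41%, 15% or 5% at 10%, 20% or 30% disengagement. Even at 20%, there is an even chance of hearing from one at most. These figures rest on equal allocation, two caregivers per family, interviews in the FSI-ECD arm only and full reachability. The disengagement rates are illustrations.

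The consequence is limited: thinner evidence on why caregivers stop attending, not a biased treatment comparison. The change is still worth making because it costs little and bears directly on an aim of the pilot.

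**What to change.** Keep eight interviews and the split of four men and four women. Before postintervention, define low attendance from the session records and include caregivers who withdrew from sessions in that group. Then draw at random within attendance strata in the FSI-ECD arm, so that some interviewees of each sex come from the low-attendance stratum where such caregivers exist. Random choice within strata keeps the protection against hand-picked informants. A fixed half of the interviews for low attenders is not needed.

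In the joint displays already planned under Data Analysis, set the interviews beside two counts from the session records: sessions completed per family and sessions attended by both caregivers. This gives the mixed methods statement in the Abstract a quantitative component on the family side.

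**Cost.** The number of interviews does not change. The eight are no longer a simple random sample, and caregivers who left have to be traced. The article does not list caregiver attendance among the tracked items, so if the existing session form does not record who was present, that field has to be added. Progression criteria are optional and not part of this recommendation.

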#### mHealth Outcomes

We will collect quantitative data on mHealth tool feasibility, acceptability, adoption, and appropriateness with CHWs and supervisors at baseline and postintervention via quantitative scales developed by researchers at Johns Hopkins Bloomberg School of Health [34]. We will track length of time to deliver FSI-ECD content, use of embedded fidelity monitoring and tracking features, and amount of CHW–supervisor contact via tablet, phone, and face-to-face. Fidelity data will include a CHW-completed electronic fidelity checklist designed to support self-monitoring and performance review with supervisors as well as a supervisor-completed electronic fidelity checklist to be completed while reviewing audiotaped FSI-ECD sessions and discussed during supervision. We will also collect data on mHealth tools postintervention via key informant interviews with CHWs (n=8) and supervisors (n=4) to understand usability of audio/video functions for FSI-ECD delivery, supervision, and quality improvement cycles.

Participant diagnostic and assessment data will be collected via tablets and deidentified. All tablets will be encrypted and password protected using a password known only to the research team. All data on the tablet will remain on the tablet until it is connected to Wi-Fi and uploaded to a secure server. Daily quality assurance and data monitoring checks will determine successful upload of the data, which will be backed up to Box, a secure, HIPAA (Health Insurance Portability and Accountability Act)-compliant, cloud-based storage platform, before it is remotely wiped from the tablet.

